## Methods

### Study design and setting

The PINO-study consists of a quasi-experimental three-arm implementation study in three comparable medium-sized Flemish (Belgium) municipalities [28]. All three municipalities have a multicultural population with around 80,000 to 100,000 inhabitants. In addition, they are all marked by a large student population due to the presence of universities or university colleges [28].

#### Municipality 1

Intervention area where GPs receive T&S embedded within a community mobilisation program.

#### Municipality 2

Intervention area where GPs receive T&S without CA.

#### Municipality 3

Support As Usual (SAU) area where GPs receive a minimal intervention that comprises an overview of the current guidelines and knowledge.

During an 18-month implementation period, GPs in the T&S area’s will receive personalised support linked to an online evaluation of their needs, views, practice organisation and EIBI-performance. This on a three-monthly base (Fig. 1).

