### Statistical methods

#### Sample size estimation

The primary research question, driving the sample size calculation, is whether the provision of tailored T&S to GPs alone or in combination with CAs will increase the early identification of hazardous and harmful alcohol use among consulting adults in general practices.

The study is powered to detect a statistically significant difference in the cumulative screening rate over the 18-month intervention period. Based on the results of the ODHIN study, we expect the intervention (tailored training and support to GPs) to achieve a rate of screening that is at least 12% or a doubling of the actual screening rate that is assumed [39]. For an alpha of 0.05 and 80% power, a total sample size of 1167 adult patients (389 in each group) is estimated.

To account for a clustering effect at the primary care practice level, with an intra-cluster correlation coefficient (ICC) set at 0.03, based on the findings of the ODHIN study, and a mean cluster size of 2256 patients (2.35 GPs per practice each seeing 960 adult patients per 3 months), the number of patients required was multiplied by 68.65 corresponding to the cluster design effect (DE = 1 + ICC (size of the cluster-1)). Thus, the final sample will consist of 80.115 patients (26.705 per arm), and 84 GPs are needed (28 in each region).

Although conclusive empirical data on the impact of CA is not available, a combined intervention-effect of the mean practice screening rate was set at 20%. This was based on practical experiences and international discussions with other researchers in the field and relates to the needed effect size to consider CA worthwhile. To detect a difference in screening rate of 8% between municipality 1 and municipality 2, we would have a power of 87%.

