### Statistical analysis plan

Baseline characteristics of the participating GP population will be compared for the 3 arms including practice (practice size, multidisciplinary practice, practice management EIBI) and GP characteristics (gender, training background, and TDF domains).

The primary outcome of the study will be the proportion of consulting adult patients screened, measured over the 18-month intervention period. The primary endpoint will be analysed according to the intention-to-treat approach. Therefore, linear regression will be used for our data analysis with early identification rates over the 18-month intervention period as a continuous outcome and the intervention group as a factor. Adding a random effect in the model will deal with clustering by general practice. The group effect will be reported as a relative risk with a 95% confidence interval. Secondary outcomes will be analysed similarly.

Subgroup analysis will allow to investigate how the primary outcome behaves in function of covariates. Here, the hierarchical nature of the data and characteristics at different hierarchy levels (i.e. characteristics of the GPs, characteristics of the practices) will be taken into consideration. Participants will be compared for primary and secondary outcomes according to changes in views as measured by TDF domains and practice organisation, taking into account the presence of CAs.

A distinction between active GP participants from less active GP participants will be made by listing those who used the AUDIT(−C) e-forms at least once versus those who did not use these forms.

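### Each arm is a single municipality, so the 80% power, the 87% power and the 95% confidence interval apply to an intervention effect only if the municipalities would otherwise screen at identical rates

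*Protocol article*

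**What the plan says.** Study design and setting describes a "quasi-experimental three-arm implementation study in three comparable medium-sized Flemish (Belgium) municipalities" and gives each arm one of them. The first is an "Intervention area where GPs receive T&S embedded within a community mobilisation program". The second has the same training and support but no community programme, and the third is the comparator, whose GPs get only an information package on guidelines.

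Sample size estimation starts from individual patients: "For an alpha of 0.05 and 80% power, a total sample size of 1167 adult patients (389 in each group) is estimated". It then inflates for one level of clustering: "To account for a clustering effect at the primary care practice level, with an intra-cluster correlation coefficient (ICC) set at 0.03". With a mean of 2256 patients per practice, the design effect is 68.65, which leads to 26,705 patients and 28 GPs per arm. The same section states 87% power for an 8-point difference between municipalities 1 and 2.

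The Statistical analysis plan section enters intervention group as a factor and adds one random effect: "Adding a random effect in the model will deal with clustering by general practice". The group effect is to be reported as a relative risk with a 95% confidence interval. The hierarchy levels named for the subgroup work are GP and practice. Municipality is not named as a source of variation.

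Aim and objectives sets out to study the added value of community actions, and Community actions says their effect will be assessed by comparing municipality 1 with municipalities 2 and 3.

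**The concern.** The practice random effect describes how practices differ within a municipality. It says nothing about how one municipality differs from another, and with one municipality per arm that difference is added in full to the group effect. Anything local that moves screening or its recording, such as local GP association activity or pandemic pressure, would be read as an effect of training and support or of community actions, with an interval that carries no allowance for it.

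The comparison of municipalities 1 and 2 is the most exposed. Community actions exist only at municipality level, this contrast is the only one that isolates their added value over training and support, and it is presented with 87% power. At stake is whether a significant result may be reported as an intervention effect or only as a difference between named places.

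**Working it through.** **Inputs from Sample size estimation.** Two-sided alpha 0.05 (sidedness is not stated, but two-sided reproduces the figure); 389 patients per group before inflation; ICC 0.03; cluster size 2256; screening rates 12% with training and support, 6% without (inferred from the doubling) and 20% with community actions added.

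**Reproducing the plan's figures**

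- Two proportions, 6% vs 12%, 80% power, continuity-corrected: 389 per group. Without the correction: 356.
- Design effect = 1 + 0.03 × (2256 − 1) = 68.65.
- 389 × 68.65 = 26,705 per arm; 1167 × 68.65 = 80,115 in total.
- 26,705 / 960 = 27.8, so 28 GPs per arm; 26,705 / 2256 = 11.8 practices per arm.
- 12% vs 20% with an effective 389 per arm: 86.2% power without continuity correction, close to the stated 87% (83.9% with it).

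Practice clustering alone accounts for the sample size and, closely, for the 87%. The variance between municipalities was therefore taken as zero.

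**Degrees of freedom.** Three municipalities minus three arm means leaves 0. The between-municipality SD, s, cannot be estimated from the trial.

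**Adding s.** The documents give no value for s, so 0.5, 1 and 2 percentage points are assumptions. With one municipality per arm:

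- Total SE = √(SE² + 2s²). Enrolling more GPs or patients shrinks SE but not 2s².
- Type I error of the planned test = 2 × [1 − Φ(1.96 × SE / total SE)].
- Power of a correctly sized test, treating s as known = Φ(difference / total SE − 1.96).

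SEs in percentage points, with 389 effective patients per arm:

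| | 6% vs 12% | 12% vs 20% |
|---|---|---|
| At the alternative, pooled rate: √(2p̄(1−p̄)/389) | 2.05 | 2.63 |
| At the null, lower rate in both arms: √(2p(1−p)/389) | 1.70 | 2.33 |
| Unpooled, used for power: √([p1(1−p1)+p2(1−p2)]/389) | 2.04 | 2.61 |

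Example for 6% vs 12%, s = 1, SE at the null: total SE = √(1.70² + 2 × 1²) = 2.21; 1.96 × 1.70 / 2.21 = 1.51; type I error 13%. With the pooled SE: √(2.05² + 2) = 2.49; 1.96 × 2.05 / 2.49 = 1.61; type I error 11%. Power: 6 / √(2.04² + 2) − 1.96 = 0.46, so 68%.

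| Assumed s (points) | Type I, 6% vs 12% (pooled; null) | Power | Type I, 12% vs 20% (pooled; null) | Power |
|---|---|---|---|---|
| 0 | 5.0%; 5.0% | 84% | 5.0%; 5.0% | 86% |
| 0.5 | 6.4%; 7.0% | 79% | 5.8%; 6.1% | 84% |
| 1 | 10.7%; 13.2% | 68% | 8.4%; 9.4% | 77% |
| 2 | 25.0%; 31.2% | 41% | 18.2%; 21.3% | 55% |

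The 84% in the first row exceeds the planned 80% because the 389 carries a continuity correction that this power formula omits.

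**A yardstick from the protocol.** An ICC of 0.03 at a 6% rate implies a between-practice SD of √(0.03 × 0.06 × 0.94) = 4.1 points. An s of 1 point is about a quarter of that SD, or (1/4.1)² ≈ 6% of the practice-level variance; an s of 2 points is about 24% of it.

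**The case against.** The strongest reply is that municipality adds no sampling variance if the comparison is confined to these three places. What remains is then confounding, which a study labelled quasi-experimental already concedes. The article leans this way: Outcomes defines the primary rate per municipality and at area level, the 87% is worded as a comparison of municipality 1 with municipality 2, and the municipalities are called comparable on population size, multicultural population and student presence. The Discussion acknowledges selection of motivated GPs and points to the control area. The size of the inflation also rests wholly on an assumed SD, and 2 points is high for areas chosen to be alike.

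Much of this stands. The conditional reading is the correct one and the figures above are a range, not an estimate. But the article does not adopt that reading. Its objectives speak of the effect and added value of the interventions, its Discussion never says that arm and municipality are inseparable, and comparability is not supported by prior screening rates.

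A reader might go further and infer four things that the documents do not support:

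- That the trial's false-positive rate is 13% or 31%. No between-municipality SD is given, so no single rate can be claimed.
- That the sample-size arithmetic is wrong. It reproduces; the fault is the level at which clustering stops.
- That a municipality random effect would repair the model. With one municipality per arm it is not identifiable.
- That a difference-in-differences analysis is ready to hand. Under EIBI data the e-form becomes available only after the GP consents, and the month-0 items under Clinical audit data are patient counts. No pre-intervention screening numerator is described, and the method would still assume parallel trends.

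**Conclusion.** The point holds in this form. The stated 80% power, 87% power and 95% confidence interval are not properties of an intervention effect in this design unless the municipalities would otherwise have identical screening rates. That conclusion, its direction and the 0 degrees of freedom follow from the allocation and need no assumption.

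The size does need one. At an assumed SD of 1 point, type I error is about 11–13% for 6% vs 12% and 8–9% for 12% vs 20%, with correctly sized power of about 68% and 77%. At 0.5 points the effect is small; at 2 points it is large. The ranges reflect whether the SE is taken at the alternative or at the null, and the power figures treat the SD as known. The data can remain as planned; what must change is what is claimed from them.

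**What to change.** 1. In Sample size estimation and in the Statistical analysis plan section, state that the 80%, the 87% and the 95% confidence interval are conditional on these three municipalities and do not cover differences between municipalities.
2. Pre-specify a short sensitivity table that adds a range of between-municipality SDs to the SE, on the scale on which the effect is reported (the article names a relative risk), and gives the SD at which significance is lost. No fixed pass mark should be set, since nothing in the documents supports one.
3. Word the conclusions, above all for municipality 1 vs 2, as differences between municipalities that cannot be fully separated from local differences.
4. Add a change-from-baseline contrast only if a comparable pre-intervention screening rate can be obtained, and state the parallel-trends assumption with it.

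Items 1 to 3 cost some wording and a little extra analysis, with no further municipalities or patients. Item 4 would need data that the article does not describe. The downside is a more cautious claim.

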## Aim and objectives

The PINO-project, which stands for Professional Involvement to reduce alcohol Negative Outcomes, aims to scale up the use of EIBI for hazardous and harmful alcohol use in general practice. This study is based on the hypothesis that training and supporting GPs, tailored to their beliefs, attitudes, and working context, together with community mobilisation may improve their EIBI performance. The PINO-project has the following objectives:
To implement and evaluate a multicomponent program comprising tailored T&S and CAs to increase the delivery of EIBI in general practice over an 18-month period.To study the added value of integrating CAs within the strategy to improve EIBI delivery in general practice.To monitor individual GPs’ progression on EIBI delivery for hazardous and harmful alcohol use on a 3-monthly basis and evaluating the effect of scaling up activities on municipal level (e.g., tailored support, CAs).To assess EIBI performance at practice level in relation to the characteristics of GPs and their practice organisation, the changes in GPs’ beliefs and attitudes and the provided support.

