##### Training

At the start of the study, GPs in municipality 1 and 2 will receive a standardised educational training based on the TDF-concepts to increase capability, motivation and opportunities for the delivery of EIBI. Here, the differences in practice organisation will be emphasized. Two booster sessions will be planned at 6 and 9 months after baseline (Table 1). These booster sessions will provide support based on changes in the TDF domains, grouping GP in relevant homogenous groups. Due to the SARS-CoV-2 pandemic, a fully online blended learning training package was designed comprising two preparatory online e-learning modules followed by two livestream sessions. If possible, the booster sessions will be performed face to face.

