### Support

The GPs will receive ongoing support through individual feedback concerning their EIBI-performance, their expressed needs and views, and practice organisation. This on 3-monthly intervals (Table 1). This well-established, evidence-based strategy for quality assurance [19] will be implemented only in the two T&S areas (municipality 1 and 2).

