##### Online GP enquiry

Four times a year, GPs will receive an online questionnaire to (Table 1):
Identify positive and negative experiencesAssess role security and therapeutic commitment of the participating GPs using the Short version of the Alcohol Attitudes Problems Perception Questionnaire (SAAPPQ) [41].Measure views based on TDF domains in relation to knowledge and skills for EIBI, personal priority setting, peer’s views, motivation, readiness for change, and emotional coping.Identify T&S needs.Obtain insights into created opportunities and changes in practice approach (e.g., case findings versus screening, targeted or universal, application of task delegation, waiting room materials, or facilitating internet access).

Every three months, an integrated dataset, linked with NHS-codes, will be created containing:
Absolute number of EIBI per age group, gender, area, and GPClinical audit data of the adult population stratified for gender and age-groups per area and GPGPs characteristics, views, experiences, practice management and needs per area and GPT&S received per GP in the intervention areas

The data will be presented as feedback to the GPs for benchmarking by area in municipality 1 and 2. In order to compare primary and secondary outcome measures, at patient counts per area level, EIBI rates will be grouped per area. Furthermore, a comparison will be made between age groups, gender, and co-morbidity since the start of the study.

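### Outcomes are compared by change in GP views with only community action (CA) named as adjustment, so the mix of arms alone can produce an association between views and screening

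*Protocol article*

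**What the plan says.** The article's Statistical analysis plan section introduces these analyses with "Subgroup analysis will allow to investigate how the primary outcome behaves in function of covariates", and then sets a comparison of GPs on both the primary and the secondary outcomes "according to changes in views as measured by TDF domains and practice organisation". The sentence ends by saying that the presence of CAs will be taken into account. No other adjustment is named there.

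The primary analysis is separate. It takes "early identification rates over the 18-month intervention period as a continuous outcome and the intervention group as a factor", with a random effect for practice. Change in views is not in that model.

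Four other places bear on the comparison:
- **Online GP enquiry:** "Four times a year, GPs will receive an online questionnaire to (Table 1"), so views are measured in the months over which the 18-month outcome accrues.
- **Training:** GPs in municipalities 1 and 2 receive "standardised educational training based on the TDF-concepts to increase capability, motivation and opportunities for the delivery of EIBI".
- **Support:** GPs receive "individual feedback concerning their EIBI-performance, their expressed needs and views", every 3 months and only in municipalities 1 and 2.
- **Aim and objectives:** the fourth objective relates EIBI performance to characteristics of GPs and practices, and to changes in "beliefs and attitudes and the provided support".

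**The concern.** A subgroup factor should be fixed before the intervention can act on it. Change in views is not. It arises after baseline, over the same period as the outcome, and T&S is built to move it. GPs with large changes will therefore come mainly from municipalities 1 and 2, where screening is also expected to be higher.

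The named adjustment does not deal with this. CA is present in municipality 1 only, so CA yes/no leaves municipality 2 (T&S) pooled with municipality 3 (minimal intervention). Within that pooled stratum, change in views partly stands in for T&S.

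A second route is possible. In the T&S areas GPs are told every 3 months how they perform, and good results could raise confidence. The outcome would then influence the grouping variable.

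At stake is the answer to the fourth objective. A positive finding could be taken to mean that changing views improves screening, or that T&S works better in GPs whose views change, when neither is true.

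**Working it through.** **The plan's own figures.** The document gives no figure for this comparison. The rates and GP numbers below come from its sample size section, which reproduces. For 6% versus 12%, two-sided alpha 0.05 and 80% power with continuity correction, n = 389 per group. The design effect is 1 + 0.03 × (2256 − 1) = 68.65. Then 389 × 68.65 = 26,705 per arm, and 26,705 / 960 = 27.8, so 28 GPs.

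**Inputs from the document.** 28 GPs per arm; 12% with T&S; 6% in the comparator (half of 12%); ICC 0.03.

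**Assumptions.** Municipality 1 is set at 12%, like municipality 2. The SD of a GP's rate is √(0.03·p·(1−p)): 5.63 points at 12% and 4.11 points at 6%. This applies the practice-level ICC to single GPs. Views have no effect on screening. T&S shifts change in views by d = 0.5 or 1 SD.

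**Step 1: arm mix only, CA as the adjustment.** The slope of rate on change in views is estimated within CA strata.
- CA absent (56 GPs, half with T&S): variance of change = 1 + d²/4; covariance with rate = d × 6/4 points.
- CA present (28 GPs): variance 1, covariance 0.
- Expected slope = 56·(6d/4) / [56·(1 + d²/4) + 28].
- d = 0.5: 42 / (59.5 + 28) = 0.48 points per SD of views.
- d = 1: 84 / (70 + 28) = 0.86 points per SD.

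The true slope is zero. Municipality 1's rate does not enter the expected slope, because the CA term absorbs it. With three-level arm the numerator is zero.

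**Step 2: false-positive rate.** The residual SD is about √[(31.7 + (31.7 + 9) + (16.9 + 9)) / 3] = 5.7 points, where 9 = 3² is the contribution of the 12% v 6% gap.
- d = 0.5: standard error 5.7/√87.5 = 0.61; ratio 0.48/0.61 = 0.79; rejection about 12%.
- d = 1: standard error 5.7/√98 = 0.58; ratio 0.86/0.58 = 1.5; rejection about 32%.

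Simulation of the same setting gives about 13% and 33% with CA only, and 5% to 6% with three-level arm. The closed form agrees within rounding and simulation error.

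**Step 3: add feedback from performance to views (assumed).** With correlation 0.3, confined to municipalities 1 and 2, and d = 0.5, GPs above the median change show about 11.4% screened and those below about 8.6%. Arm adjustment does not remove this. In a separate simulation in SD units (arm effect 1.0, shift 0.5, feedback coefficient 0.3 in the T&S arms), the false-positive rate was 86% without arm in the model and still 44% with arm.

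**Step 4: the primary comparison.** In those SD-unit simulations the arm effect from a model without change in views stayed at 1.00 throughout.

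**The case against.** **The analysis is exploratory.** The Abstract speaks of exploring a correlation, and the fourth objective is worded as a relation. A reader might infer that the trial intends a causal estimate of views on screening; the document does not say so. This stands and limits the weight of the point. It does not remove it. An association produced by arm mix says nothing about views beyond the fact that T&S moved both, and the subgroup heading invites reading it as effect modification.

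**T&S exposure may be in the model after all.** The Outcomes section relates secondary outcomes to provided support as well, the quarterly dataset records the T&S each GP received, and an unseen SAP may specify the model. This stands in part: nothing excludes arm. But the sentence that sets this comparison does name an adjustment, and the one it names is insufficient.

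**Reverse causation is not established.** A reader might infer that the result is biased because feedback raises views. No passage shows that it does; the 0.3 is assumed, and the route is absent in municipality 3. This stands, so the arm-mix argument, which needs no feedback, carries the point.

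**The T&S effect is not shown to be understated.** Adjusting the arm effect for change in views would shrink it under feedback, and a reader might take that as a flaw in the trial's main result. No such adjusted effect is planned.

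**The cut is not in the document.** The median split is only a way to display size. The slope results do not depend on it.

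**Conclusion.** The point holds for this one exploratory comparison. As worded, it uses a post-baseline variable that T&S targets, and its only named adjustment does not separate T&S from no T&S. With no effect of views on screening, it can give a spurious association in about 13% to 33% of trials, against about 5% to 6% with three-level arm. Those figures rest on the protocol's 12% and 6%, on 28 GPs per arm, and on an assumed T&S shift in views of 0.5 to 1 SD. If T&S does not move views, the problem vanishes; a larger shift makes it worse. Feedback from performance would add reverse causation that arm adjustment cannot remove, but its presence and size are assumptions. The primary intention-to-treat group effect is not affected. The wording should be corrected before the data are analysed.

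**What to change.** 1. **Subgroups.** Define effect-modifier analyses by baseline TDF domains, baseline SAAPPQ and baseline practice organisation, each tested by interaction with arm. TDF domains and practice characteristics are already listed for the baseline comparison.
2. **Change in views.** Take this out of the subgroup heading. Relate change up to quarter q to the screening rate in quarter q+1, adjusted for the rate in quarter q and for arm at three levels instead of CA yes/no. Use quarter-specific rates: the cumulative rates in the Outcomes section at q+1 contain the data up to q. Treat change in practice organisation in the same way.
3. **Reporting.** State that the result is an association and not an effect of views on screening.

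The cost is a few lines in the SAP and one quarterly model. The data are already collected every 3 months by GP. One quarter is lost to the lag and precision is somewhat lower. The lag and the adjustment for the current rate reduce reverse causation but cannot rule it out, which is why the label matters.
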